## **6. Execution of the study**

### **6.1. Preliminary check-up**

Interested persons will be written and orally informed about the aim, procedure, risks and duration of the study. After written consent a blood sample for genotyping is taken. For this reason 9 ml of venous EDTA blood is taken. If the participant is a carrier of a wanted genotype an appointment for a preliminary check-up is arranged. At this preliminary check-up a physical check-up is made and laboratory parameters are analyzed from blood giving information on the health status of the participants. Following parameters will be determined: Blood cell count, creatinine, bilirubin, GOT, GPT,  $\gamma$ GT and a pregnancy test for women. According to the results a decision on inclusion in the study is made.

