### **6.6.3 Candidate gene analysis**

Variants in genes, which probably influence nutrikinetic or the effect of EGCG according to literature or could at least be involved due to biological plausibility, are analyzed. In a first step we will analyze known functional variants as well as gene variants with common alleles or haplotypes. We will analyze genes like Catechol-O-Methyltransferase (COMT), OATP1A2, -1B3 and other relevant transport proteins. Further we will analyze genes coding for glucuronyltransferases, and if we see significant effects of EGCG on oxidative stress, inflammation or cardio-vascular parameters we may also analyze genes related to this effects.

To identify new polymorphisms in genes which are yet not well characterized like OATP1B3 we plan to systematically sequence the coding and bordering non-coding regions of the gene

including 5'- und 3'-regions in a sub population of our participants. If we can detect such mutations we will establish specific genotyping assays.

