## **7. Statistical analysis**

### **7.1. General**

It is the aim of this study to investigate in vivo the influence of genetic polymorphisms in COMT, OATP1A2, OATP1B3 and further molecules involved in EGCG effect on the kinetics of EGCG. It should be tested if plasma-concentration-time profiles (AUC, Cmax, and oral clearance) differ in relation to the genotype.

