## **7.4 Sample size estimation**

With a sample size of n=100 it is possible to detect genetic variation with an allele frequency of 5% at least once with a level of significance of 5%.

Assuming a frequency of 20% of carriers of the methionine variant (heterozygote plus homozygote carrier) and an allele frequency of 11% for the COMT polymorphism an effect on the pharmacokinetics would be detectable in n=100 participants. It had been shown that a mean AUC of 1403 ng/ml h with a standard deviation of 632 can be detected after multiple dosing of 200mg EGCG in n=9 participants [8]. If n=20 participants carry either Val/Met or Met/Met genotypes and n=80 carry Val/Val genotype a difference of 30% and more in the oral clearance of EGCG could be detected with a power of 80% and a significance of 0.05 (sample size calculated with nQuery Advisor 4.0).

In addition, with the estimated sample size of n=100 it is possible to determine the distribution of nutrikinetic parameters of EGCG in healthy participants and give evidence if there are sub-populations showing a poor absorption or fast metabolism or a good absorption and a poor elimination of this substances.

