## **7.5 Statistical methods:**

The results will be analyzed using non-parametric Jonckheere Terpstra Trend Tests based on the estimation of a trend in the EGCG kinetics in carriers of wild type > heterozygote > homozygote.

Wild type and homozygote carriers will be compared with parametric t-test. This study is of exploratory nature. A significant association detected by testing individual factors is suggested to be important, even if it is no longer significant after adjusting to multiple testing. This study is to our knowledge the first trial studying the genetic variability of green tea catechin EGCG and has the characteristics of a pilot study.

AUCs will be calculated using non-compartmental analysis as well as population kinetic modeling. An experimental analysis with calculation of median, mean, variance and graphic presentation in Box-Plots will be conducted.

Participants discontinuing the study or fulfilling exclusion criteria will be marked as drop-out and will be excluded from nutrikinetic analysis.

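### If more than one gene decides who is invited, one-gene-at-a-time tests are confounded by the other selection genes; one joint model removes this at little cost

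*Protocol*

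**What the plan says.** Section 6.1 takes the genotyping sample after consent and continues: "If the participant is a carrier of a wanted genotype an appointment for a preliminary check-up is arranged". It does not say which gene or genes count, which variants, or how many participants of each are sought. The inclusion criteria in 4.2 contain no genotype.

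Several genes are under study. Section 7.1 sets out to "investigate in vivo the influence of genetic polymorphisms in COMT, OATP1A2, OATP1B3 and further molecules", and 6.6.3 keeps the list open: "We will analyze genes like Catechol-O-Methyltransferase (COMT), OATP1A2, -1B3 and other relevant transport proteins". The primary outcome in 7.2 compares oral clearance between variant carriers and wild type in general, not for COMT alone.

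Section 7.5 names two genotype tests: "The results will be analyzed using non-parametric Jonckheere Terpstra Trend Tests" and "Wild type and homozygote carriers will be compared with parametric t-test". Each handles one gene at a time and carries no covariate. Population kinetic modelling appears only as a way to calculate AUC. The reading rule is "A significant association detected by testing individual factors is suggested to be important", even where significance is lost after multiplicity adjustment.

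Section 7.4 plans on 20 COMT variant carriers and 80 Val/Val among 100 participants, a split taken from an assumed population frequency: "Assuming a frequency of 20% of carriers of the methionine variant".

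**The concern.** Unlinked genes are independent in the source population. They stop being independent once people are enrolled for carrying a variant in either of two genes. A participant without the COMT variant is then more likely to be in the study because of an OATP variant, so the COMT wild-type group holds more OATP carriers than the COMT carrier group does. If the OATP variant changes clearance, the simple COMT contrast picks up part of that effect.

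This differs from whether the sample represents healthy people, and from imbalance in sex or body size. The carrier versus wild-type contrast itself is disturbed by the other study genes, and demographic adjustment would not repair it. At stake is the primary comparison: a gene without effect can look active, or a real effect can be diluted, and 7.5 would take the single-factor result at face value.

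**Working it through.** **The plan's own figures (7.4).** An allele frequency of 11% gives 1 − 0.89² = 20.8% carriers, consistent with the stated 20%. The coefficient of variation is 632/1403 = 0.450. For 20 v 80 and a 30% difference on the raw scale, the standard error is 0.450 × √(1/20 + 1/80) = 0.113. Two-sided power is Φ(0.30/0.113 − 1.96), about 76% (75% with the t distribution), against the stated 80%. On the log scale a ratio of 0.7 gives 91%. The point below does not depend on this figure.

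**Inputs from the protocol.** n = 100; COMT carrier share 20%; log SD = √ln(1 + 0.450²) = 0.43. With a fixed dose, log clearance has the same SD as log AUC.

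**Assumptions (not in the protocol).** COMT has no effect. Each OATP variant lowers clearance by 30%, so −ln 0.7 = 0.357 on the log scale. Carrier shares are 20% for one OATP gene (schemes 4 and 5) or 10% each for OATP1A2 and OATP1B3 (schemes 1 to 3). All quotas are assumed.

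**Formula.** Spurious log difference for COMT = 0.357 × (mean OATP variants per COMT non-carrier − mean per COMT carrier).

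1. *Quotas filled without regard to the other genes:* 20 COMT, 20 OATP1A2 and 20 OATP1B3 carriers, and 40 with no variant. The OATP quotas bring in 40 × 0.2 = 8 further COMT carriers. Carriers: (20 × 0.2 + 8 × 1.1)/28 = 0.457. Non-carriers: (32 × 1.1)/72 = 0.489. Difference 0.032 × 0.357 = 0.011, ratio 1.01.
2. *As 1, but the last 40 are only COMT wild type:* non-carriers (35.2 + 40 × 0.2)/72 = 0.600. Difference 0.143 × 0.357 = 0.051, ratio 1.05.
3. *Mutually exclusive quotas, 20/20/20/40:* COMT carriers are barred from both OATP quotas and OATP1A2 carriers from the OATP1B3 quota. Carriers: 0.20. Non-carriers: (20 × 1.1 + 20)/80 = 42/80 = 0.525. Difference 0.325 × 0.357 = 0.116, ratio 1.12. A true 30% COMT reduction would read as exp(−0.357 + 0.116) = 0.79, a 21% reduction.
4. *50 carriers of either of two 20% variants plus 50 with neither:* 0.308 v 0.20, difference 0.108 × 0.357 = 0.038, ratio 1.04.
5. *Only carriers of either of two 20% variants:* every COMT non-carrier has the OATP variant, against 20% of COMT carriers. Difference 0.8 × 0.357 = 0.285, ratio 1.33.
6. *Selection on one gene, or none:* difference 0.

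| Scheme | COMT share | Spurious ratio | False positives, single-gene test |
|---|---|---|---|
| 1 | 28% | 1.01 | about 5% |
| 2 | 28% | 1.05 | about 7% |
| 3 | 20% | 1.12 | about 16% |
| 4 | 28% | 1.04 | 6–7% |
| 5 | 56% | 1.33 | about 88% |
| 6, no gate | 20% | 1.00 | 5% |

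The error rates come from simulated studies of 100 participants. In scheme 3, power for a true 30% COMT reduction is about 55% with the single-gene test (49 to 55% across runs and tests) and about 88% with a joint model. In every scheme the joint model returned a ratio of 1.00 for the inactive gene, with about 5% false positives. With no gate it lost nothing: 89–91% power, against 81–88% for the single-gene tests.

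**Correlation.** Let carriers of either of two 20% variants always be enrolled, and carriers of neither with probability s. The correlation between the genes is 0 at s = 1, −0.30 at s = 0.25, −0.51 at s = 0.1 and −0.80 at s = 0. The COMT carrier share rises from 20% to 38%, 47% and 56%.

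**The case against.** The strongest objection is that the trigger is not documented. Section 6.1 names no gene and no quota, and other text points away from multi-gene selection. The 20/80 split in 7.4 comes from a population frequency, as in unselected sampling. Section 4.2 lists no genotype. Section 6.5 takes genotyping blood at the preliminary check-up, the visit that 6.1 places after genotyping. Variants found later by sequencing (6.6.3) cannot have guided invitations, and unlinked variants not used for selection are unaffected. Section 2.3 says the effect of OATP variants on EGCG transport has not been studied. All of this stands, and it is why the point is conditional.

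A reader might infer that the primary comparison is confounded as planned, with false positives near 88%. The documents do not support that. The figure belongs to a carriers-only study with 0.20/0.36 = 56% COMT carriers, which does not fit the 20% in 7.4. It is an upper bound. The 12% figure does keep 20/80, but it needs mutually exclusive quotas that the protocol does not describe.

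It can also be said that the rule in 7.5 concerns multiplicity, that the study is exploratory, and that model covariates may be left to an analysis plan that is not shown. The first is a fair reading of that sentence. The exploratory label excuses unadjusted significance levels but does not remove bias from a contrast. On the third, the protocol itself fixes the tests, so the point concerns a stated choice rather than an omission.

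**Conclusion.** The point holds in conditional form. If 6.1 selects on more than one gene on an either/or basis, the single-gene tests of 7.5 are confounded by the other selection genes. If it selects on one gene or none, or fills genotype combinations in proportion, they are not. The protocol does not say which applies.

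Under the assumptions above, the spurious COMT difference runs from about 1–5% with near-nominal error to about 12% with 16% false positives and a loss of power from about 88% to 55%. OATP carrier rates, OATP effects and quotas are all assumed, so this is a range and not an estimate for this trial. The joint model is unbiased in every scheme tried and gives up no power when there is no gate. It is a cheap improvement rather than a correction of a demonstrated error.

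**What to change.** - **Section 6.1:** state which genotypes are wanted, how many of each, and whether a person already counted for one gene can fill another gene's quota. Reconcile this with the 20/80 split in 7.4, the inclusion criteria in 4.2 and the timing of the genotyping sample in 6.5. If only one gene or none is used, saying so settles the matter.
- **Section 7.5:** read each gene's effect on log oral clearance from one linear model that contains every variant used for selection, as allele count or carrier status. Keep the Jonckheere-Terpstra and t-tests as descriptive, or stratify them by the other selection variants.
- **CRF:** record which genotype led to each invitation.

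The cost is a few sentences and one data field, with no extra participants or assays. The downside is one or two degrees of freedom per variant, and a wider interval where selection makes two variants nearly exclusive.

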## **8. Safety – Risk for Participants**

### **8.1 Study drug**

For this study, a commercially available green tea extract with an EGCG content of 50% is used. Green tea extract is a nutrition supplement and no medical product. EGCG is the active substance of green tea extract. It is usually consumed as green tea or black tea beverage or it can be bought in drug stores or on the internet as nutrition supplement capsules (e.g. [name] capsules or BTC Vcaps).

### **8.2 Amount of drug**

For this study 150mg of EGCG per capsule is twice daily used (300mg per day and participant). This is the amount which is usually the content of 3-5 cups of green tea every day.

### **8.3 Possible risks and adverse events**

Adverse effects of green tea extract are described as rare events during long intake. No adverse effects have to be expected during 5 days of EGCG intake. Case reports reported a development of changes in the level of liver enzymes in the context of food or food supplement containing green tea [14]. From 216 reports about adverse events in temporal relation to the intake of food containing green tea, only in 7 cases a causal relation between increase of transaminases and the intake of green tea extract was plausible. The main compound EGCG seem to be causable as in experiments EGCG show a 10-time higher cytotoxicity on isolated rat liver cells than other catechins [15].

The dosage of 300mg EGCG used in this study which is equal to 4-7 cups of green tea every day is not associated with any known adverse event.

In a dose-finding study for EGCG 33 patients with stable remitted CLL were treated over 6 month with 400 and 2000mg daily. In this study grade 3 toxicity was observed in 2 Patients, in one case from diarrhea in the other case from abdominal pain [16].

### **8.4 Blood sampling**

The risks of venous blood sampling are the occurrence of mild pain, bleeding or hematomas. Extremely rare but in principle possible are infection complications at the puncture, nerve injury or strong bleeding due to arterial puncture. These complications are very rare and in our practical experience such serious complications never happened in more than 1000 cases of venous blood sampling.

In principle, allergic reactions can occur due to all used materials, irritation caused by adhesive plaster is relative common. A disposition to allergic reaction will be inquired and considered if necessary.

### **8.5 Physical activity during study day**

During study day the participants are free to move, but they should sit or lay down during blood sampling.

### **8.6 Eating and drinking during study.**

One day before the study day participants should not drink tea, especially green tea. A list containing information about food which could contain EGCG or similar compounds is given to the participants ahead of study.

Participants must not eat from 22:00 the day before the study day until two hours after the intake of the study drug at study day. Afterward the participants get a bread roll, lunch and dinner during their stay on the research ward at study day. For the choice of the dish, attention will be payed that the food does not contain EGCG or similar substances. For drink participants get mineral water.

Because it is known that nutrikinetic of EGCG is influenced by food intake (more than 3-times higher blood levels under fastened then fed conditions) participants should not eat additional food. No more than 3L of water is allowed to be drunk during study day

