### 2.2 Nutrikinetics of EGCG

EGCG is quickly absorbed after oral administration (capsule) and reaches the maximal blood concentrations after 1-2 hours. After single dose administration of 400mg EGCG capsules maximal plasma concentration of 112ng/ml and an AUC of 623ng/ml\*h was measured, after a single dose of 800 mg EGCG 438ng/ml and an AUC of 2779 ng/ml\*h was determined [6]. The half-life time of EGCG in plasma is 2-4 h. The intake of 400 mg and 800 mg over 4 weeks does not lead to any accumulation (under multiple dosing values measured 24 h after the last administration were below limit of detection), because the half-life time is too short (see figure1). Nevertheless AUC of a 800 mg doses was 60% under multiple dosing than single dosing. This might be due to an inhibition of presystemic intestinal metabolism. Splitting 800mg/day into several single doses leads therefore to higher blood levels than a single dose [7-9]. EGCG can be found mostly unbound in the plasma (92%), is biliary eliminated and can be neither detected in its conjugated nor glucuronidated form in urine [7-9]. In figure 3 the time-plasma concentration profiles after administration of 800mg and 400mg EGCG capsules are presented. Dots represent the profile after single dose (“before”), triangles represent the profile after 4 weeks of intake (“after”).

[figure not shown]

**Fig. 1:** Plasma concentration profiles after administration of 800mg and 400mg EGCG capsules after single doses (dots) and 4 week soft intake (triangles) Fig. from ref. [7].

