### **6.3. Study Procedure**

Day 1-4:

Participants get for four day in the morning and with a gap of 12h in the evening one capsule with 150mg EGCG respectively 300mg EGCG per day. They are asked to take the capsule with breakfast or dinner with one glass of tap water.

Study day:

At study day, participants appear in the morning under fasting conditions at the research ward. After a short physical check-up, a venous line is established and a blood sample for the basal level of kinetics is taken. The participants take one capsule with 150mg EGCG with one glass of tap water. In the following ten hours blood samples for the analysis of the EGCG plasma concentration is taken. After 4h and 10 h participant get a meal and a snack. No other food is allowed during their stay on the research ward.

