#### **6.6.4 RNA-isolation and gene expression analysis**

Total RNA is isolated from blood sample using standard methods (Ficoll cell separation, Qiagen RNeasy Mini Kit, Pax-Gen). It is planned to investigate if the expression of genes of the drug transport, metabolism, cell growth, generation or detoxification of reactive oxygen species is changed by a 4-day treatment with EGCG. Expression of candidate genes is quantified using qPCR (Sybr Green, TaqMan). In this respect, as for the genetic analysis, participants were asked to consent in a genome-wide analysis. In this case common Affymetrix Expressions-Microarrays should be used. In addition to RNA, gene expression differences will also be semi-quantitatively on protein level using western blot. For this reason protein fractions are isolated from isolated lymphocytes and frozen at -80°C.

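### Tea is restricted only on the day before the study day, so the run-in does not standardise EGCG exposure to the 300 mg daily that the aim names; the effect on clearance is possible but not shown

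*Protocol*

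**What the plan says.** Section 3 sets the aim: EGCG kinetics after four days of multiple dosing at 300 mg per day, compared between genotypes. Section 6.3 gives the run-in dose: "Participants get for four day in the morning and with a gap of 12h in the evening one capsule with 150mg EGCG". The scheme in 6.4 labels these days -4 to -1 and has participants keep a diary of capsule intake and adverse events.

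Dietary control is in section 8.6:
- Tea: "One day before the study day participants should not drink tea, especially green tea".
- Food: "A list containing information about food which could contain EGCG or similar compounds is given to the participants ahead of study". No instruction and no period is attached to the list.
- Study day: ward food is chosen to be free of EGCG, and "For drink participants get mineral water".

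Sections 4.2 and 4.3 do not exclude habitual tea drinkers, and 6.3 sets no tea limit for the days at home.

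The protocol gives the tea equivalent of the daily dose twice. Section 8.2: "This is the amount which is usually the content of 3-5 cups of green tea every day". Section 8.3: "The dosage of 300mg EGCG used in this study which is equal to 4-7 cups of green tea every day".

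Section 2.2 reports a plasma half-life of 2-4 h and no accumulation at 400 or 800 mg over four weeks. It also reports that the AUC of an 800 mg dose differed by 60% between multiple and single dosing (the word giving the direction is missing; the text that follows implies higher), and comments: "This might be due to an inhibition of presystemic intestinal metabolism".

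**The concern.** The run-in exists to bring every participant to one defined multiple-dose state before sampling. The protocol takes care over this elsewhere: a single capsule batch, a diary to support compliance, and controlled food and drink on the study day. Yet for three of the four run-in days the same compound may be drunk freely and without record, in amounts that the protocol itself puts on a par with the capsules.

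Section 2.2 raises the possibility that earlier exposure alters presystemic metabolism, which could outlast EGCG in plasma. If so, unequal tea intake would add between-person variance to oral clearance, the primary outcome, in a comparison that expects only about 20 carriers. Tea intake that was not recorded cannot be reliably recovered afterwards.

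**Working it through.** **1. The plan's own power figure.** Section 7.4 gives mean AUC 1403 and SD 632 ng/ml h, groups of 20 and 80, a 30% difference, alpha 0.05 (sidedness not stated) and 80% power.
- Difference: 0.3 × 1403 = 420.9. Standard error: 632 × √(1/20 + 1/80) = 158. Ratio: 2.66.
- Power (noncentral t, 98 df): 75.1% two-sided, 84.1% one-sided. The stated 80% is not reproduced exactly. The two-sided 75.1% is the baseline below.

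**2. Can tea match the capsules?** EGCG per cup = 300 mg / cups.
- 8.2: 300/5 to 300/3 = 60-100 mg.
- 8.3: 300/7 to 300/4 = 43-75 mg.
- On either figure, 3-7 cups a day supply another 300 mg.

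**3. Run-in totals.** Capsules: 4 × 300 = 1200 mg. Tea on days -4 to -2 adds 3 × (mg per day).

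| Tea, mg/day | Run-in total, mg | Ratio to 1200 |
|---|---|---|
| 0 | 1200 | 1.00 |
| 100 | 1500 | 1.25 |
| 150 | 1650 | 1.375 |
| 300 | 2100 | 1.75 |

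**4. Direct carry-over.** Fraction left = 0.5^(t / half-life), with half-life 2-4 h (2.2).
- t = 24 h: 0.02% to 1.6%.
- t = 32 h: at most 0.4%.

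Only an altered metabolic state could carry an effect to the study day.

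**5. Illustrative effect on power.** Assume a share f of tea drinkers whose AUC is multiplied by r. Neither value is in the protocol.
- CV = 632/1403 = 0.450. Variance of log clearance = ln(1 + 0.450²) = 0.185.
- Added variance = f(1 − f)(ln r)². The SD in step 1 is inflated by the square root of the variance ratio.

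| f | r | Added variance | Variance ratio | Two-sided power |
|---|---|---|---|---|
| 0.3 | 1.1 | 0.0019 | 1.01 | 74.7% |
| 0.5 | 1.1 | 0.0023 | 1.01 | 74.6% |
| 0.3 | 1.3 | 0.0145 | 1.08 | 71.9% |
| 0.5 | 1.3 | 0.0172 | 1.09 | 71.3% |
| 0.3 | 1.6 | 0.0464 | 1.25 | 65.5% |
| 0.5 | 1.6 | 0.0552 | 1.30 | 63.9% |

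The rows with r = 1.6 borrow the 60% from 800 mg over four weeks and are a ceiling, not an estimate.

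**6. Does the scale matter?** Step 5 applies a log-scale variance ratio to a raw-scale power. Done wholly on the log scale with r = 1.3, power goes from 67.6% to about 64% for a clearance ratio of 1.3, and from 90.8% to 88-89% for a ratio of 0.7. The loss is 2 to 4 points either way.

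**The case against.** The strongest reply is that sampling is already protected. EGCG clears within hours, section 2.2 reports no accumulation, and everyone has a tea-free day with capsules only before the study day. All of that stands, and it rules out direct carry-over.

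The 60% figure is also the wrong contrast. It compares single with multiple dosing at 800 mg over four weeks. Here every participant has already had four days of capsules, and the contrast is 300 against perhaps 600 mg per day on three days, then 300 mg on day -1. The protocol gives no AUC change for that and none for 400 mg. The mechanism is offered tentatively, with no time course of reversal. This stands too: a reader might infer that free tea makes the multiple-dose state differ on the study day, but the documents show only that it could.

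A reader might also infer that tea can pass for a genotype effect. With 20 versus 80, chance imbalance in the share of tea drinkers has a 95% range of 1.96 × √(f(1 − f)(1/20 + 1/80)), or 22-25 percentage points for f = 0.3-0.5. At r = 1.3 that is a spurious difference of about 6-7%. This is ordinary random error, already counted in the variance term. The protocol gives no reason to expect tea intake to follow genotype.

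The SD of 632 comes from a cited study whose diet control the protocol does not describe, so some tea-related variation may already be in it. The food list may be meant to cover the run-in, but without an instruction or a period it does not do so as written. Finally, section 7.5 calls the study exploratory, which lowers the stakes without making the gap useful.

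**Conclusion.** The point holds as a minor one. As written, the run-in does not standardise EGCG exposure: tea on days -4 to -2 can double the daily amount on those days and raise the run-in total to 1.75 times the capsule dose. A reader might take the doubling to apply to the whole run-in; it does not, because 8.6 bars tea on day -1.

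An effect on study-day clearance is possible but not shown, and its size at 300-600 mg per day is unknown. With 30-50% tea drinkers and an AUC shift of 10-30%, both assumed, two-sided power falls from about 75% to 71-75%. The 64% reached with a 60% shift is only a ceiling. The consequence is added variance, and bias arises only if tea intake differs by genotype.

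The point should not be rested on gene expression. Section 6.6.4 asks whether expression "is changed by a 4-day treatment with EGCG", but the baseline RNA sample is taken at the preliminary check-up, before the first capsule. A restriction starting on day -4 leaves tea before that sample uncontrolled, so tea withdrawal in habitual drinkers would still be mixed with the capsule effect.

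Separately, 8.2 and 8.3 give different cup counts for the same 300 mg and must be reconciled.

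**What to change.** In section 8.6:
- Extend the tea restriction to the whole run-in, from day -4 to the end of the study day.
- State that the food on the list already handed out is to be avoided over the same period.
- Have participants record any tea in the diary they already keep, for use as a covariate or in a sensitivity analysis of oral clearance.

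The cost is three more days without tea for participants, a sentence or two in 8.6 and one more diary entry. No visit, sample or staff time is added, and no stated sample size or power figure changes. With full adherence, tea adds nothing to the 1200 mg run-in total from the capsules; where adherence fails, the diary allows adjustment. The change does not control tea before the baseline RNA sample, so it should not be presented as solving the expression question.
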